### 6.3.2 Accrual and follow-up

Inclusions will be described.

Deviations from eligibility criteria and protocol (withdrawals, loss to follow-up, randomisation treatment discontinuation and replacement treatment, visits et phone interviews undone) will be described.

### 6.3.3 Baseline characteristics

Characteristics of included participants will be described.

Endpoints and changes in endpoints from D0 will be described at each visit (D7, D14 and D28) or phone interview (D3, D5, D9 and D12).

### 6.3.4 Primary outcome for participants not taking ACEI or ARB before inclusion

The primary endpoint will be described at each visit and phone interview, as a binary outcome and a time-to-event outcome.

The primary analysis is the set of interim and final analyses on the primary endpoint at D14 (futility and efficacy).

Secondary analyses of the primary endpoint will explore variants of the primary analysis, concerning:

- Management of randomisation treatment discontinuation: on treatment, per protocol, as treated
- Management of missing values: worst case, inverse probability weighting
- Primary endpoint at D7

The sensitivity analysis will repeat the primary analysis at D28 to confirm the results of D14.

### 6.3.5 Primary outcome for participants taking ACEI or ARB before inclusion

If, following a decision from the DSMB, sample size has been increased to reach a power sufficient for clinically relevant statistical tests, the statistical analysis will repeat the one in the stratum of participants not taking ACEI or ARB before inclusion.

Conversely, if the size has remained the same, the analysis will be descriptive only.

In both situations, if the Telmisartan arm shows no efficacy during futility (arm discontinuation) or efficacy analyses in the stratum with participants not taking ACEI or ARB before inclusion, both strata will be pooled in a single analysis.

### 6.3.6 Secondary endpoints

The analyses on the secondary endpoints will be performed on intention-to-treat on available data, except for safety analysis.

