### 3.2 Secondary objectives

The study's secondary objectives are:

- Appraise the efficacy of several experimental treatments of SARS-CoV-2 infection, compared with standard of care, to prevent death on Day 28
- Appraise the efficacy of several experimental treatments of SARS-CoV-2 infection, compared with standard of care, to prevent hospitalisation on Day 28
- Appraise the efficacy of several experimental treatments of SARS-CoV-2 infection, compared with standard of care, to prevent admission to intensive care unit on Day 28
- Appraise the efficacy of several experimental treatments of SARS-CoV-2 infection to eliminate nasopharyngeal carriage of the virus, compared with standard of care
- Appraise the efficacy of several experimental treatments of SARS-CoV-2 infection, compared with standard of care, to prevent loss of autonomy
- Appraise tolerance of experimental treatments against SARS-CoV-2 infection
- Study those factors associated with clinical deterioration in patients with COVID-19
- Evaluate the feasibility and acceptability of the trial and model of care model implemented.
- Evaluate the relationship between concentrations for each drug and efficacy of each of the treatments

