#### 4.3.2 Secondary criteria

- Hospitalisation proportion and its causes between Day 0 and Day 28 within each group
- Proportion of deaths and their causes between Day 0 and Day 28 within each group
- Intensive care hospitalisation proportion and its causes between Day 0 and Day 28 within each group

---

 Currently, the following criteria are being proposed: SpO2 < 92% in ambient air or 4% reduction in SpO2 since inclusion; respiratory rate > 30 min; heart rate > 130/min; systolic blood pressure < 90 mmHg or diastolic < 60 mmHg; other parameters indicating hospitalisation, in the judgement of the attending physician (for example, unexplained fall, severe digestive problems, reoccurrence or persistent fever > 38.5°C etc.)

- Proportion of patients with a reversion of SARS-CoV2 RT-PCR on a nasopharyngeal swab on Day 7 and Day 14, in each group
- Proportion of patients with a loss of autonomy evaluated by ADLs and IADLs on Day 14 and Day 28
- Changes in CBC, inflammatory markers (please see paragraph **Erreur ! Source du renvoi introuvable.**) and immunological markers (please see paragraph **Erreur ! Source du renvoi introuvable.**) from Day 0 to Day 7 and Day 14 in each group
- Number and proportion of adverse events of grades 1, 2, 3, 4 between Day 0 and Day 14 in each group
- Number and proportion of adverse reactions of grades 1, 2, 3, 4 between Day 0 and Day 14 in each group
- Plasma trough concentration of experimental drugs in the study on Day 7
- Acceptability of the treatment

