#### 5.3.6 Face-to-face visits (Day 7 and Day 14)

- Face-to-face visits shall be carried out in the participant's home by the trial's mobile team.
- Face-to-face visits are to consist of:
  - Interview and clinical examination (including the recording of undesired effects)
  - Taking of drugs
  - SpO2
  - Blood sampling
  - Nasopharyngeal swab for SARS-CoV2 RT-PCR
  - Advice

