## 6 Statistical analysis

- Inclusion and exclusion from statistical analysis

Participants who died, were lost to follow-up or withdrew consent will be included in the analysis. Participants with at least one of the following conditions could be excluded:

- Having never taken trial treatment or ignoring the allocated arm
- Included without signing a consent form
- Included despite non-compliance with at least one major eligibility criterion
- Having withdrawn consent

The SAB will review cases documentation collected by the trial team and will take an exclusion decision blinded of the randomisation arm and the participant's post inclusion evolution.

Major deviations from eligibility criteria are defined as any deviation on the following criteria:

- Positive SARS-CoV-2 RT-PCR
- Age  $\geq$  65 years

Randomisation treatment discontinuation will be managed as follows:

- On intention to treat (ITT)  
Any participant will be analysed in the allocated arm, disregarding eligibility deviations or non-compliance with randomisation treatment.  
All data will be used.
- On treatment (OT)  
Any participant will be analysed in the allocated arm, irrespective of eligibility deviations or non-compliance with randomisation treatment.  
All data observed after discontinuation of randomisation treatment will be dropped.
- Per protocol (PP)  
Any participant will be analysed in the allocated arm, irrespective of minor eligibility deviations or minor non-compliance with randomisation treatment.  
All data from any participant with a major eligibility deviation or a major non-conformity with randomisation treatment will be dropped.
- As treated (AT)  
Any participant will be analysed with respect to the actually received treatment, irrespective of the allocated treatment.

Missing values will be managed as follows:

- Analysis on available data (AD): any missing value will be ignored.
- Missing as failure (M=F) procedure: any missing value will be analysed as a failure (main endpoint: disease worsening)
- Worst case procedure (WC):  
First sub-analysis: Any missing data is analysed as a success in the first arm, and as a failure in the second arm.  
Second sub-analysis: Any missing data is analysed as a failure in the first arm, and as a success in the second arm  
The conclusion will be that of each sub-analysis if they are identical.
- Inverse probability weight (ITW) procedure:  

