## 6.1 Principles

The primary endpoint is the by-arm rate of hospital admission or death between D0 and D14 (binary outcome in the primary analysis)

The primary endpoint analysis consists in multiple sub-analyses with multiple arms, multiple stages (sequential analyses) and procedures to manage randomisation treatment discontinuation or missing values. Tests multiplicity due to multiple stages will be managed by alpha spending function methods.

This trial is an adaptive phase III trial. Sequential analyses will be performed for the primary endpoint at D14 (and D28 for the last one) with different objectives:

- Interim analysis n°1: futility at D14
- Interim analysis n°2: futility at D14
- Interim analysis n°3: futility and early efficacy at D14
- Primary analysis: demonstrated efficacy at D14
- Sensibility analysis: maintained efficacy at D28

Each analysis on the primary endpoint will be on intention-to-treat with "missing as failure" (ITT-M=F).

Each experimental arm will be independently compared to the control arm, which leads to several paired tests.

Management of withdrawal or addition of an arm during trial:

- Arm withdrawal  
If an interim analysis demonstrates that it is useless to continue with an experimental arm compared to the control arm, this arm is discontinued and the trial continues with the other arms.

If an interim analysis demonstrates the early efficacy of an experimental arm compared to the control arm, this arm becomes the new control arm and the former control arm is discontinued. Either the SAB and the sponsor decide to definitively stop the trial, or a protocol amendment describes the implications regarding trial conception and statistical analysis, especially the comparison between the new control arm with the other arms.

- Arm addition

If a new medicine is deemed interesting after the trial started, a new arm is added. A protocol amendment describes the implications trial conception and statistical analysis, especially the comparison between the new arm with the control arm.

The primary analysis will be performed in the strata of participants not taking renin-angiotensin system blockers (ACEI or ARB) before inclusion, if the Telmisartan arm is maintained up to the end of the trial.

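### Participants who die drop out of the loss-of-autonomy denominator, so this efficacy comparison is made among survivors only and can understate, hide or reverse a benefit

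*Protocol*

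**What the plan says.** Section 3.2 lists as an efficacy objective: "Appraise the efficacy of several experimental treatments of SARS-CoV-2 infection, compared with standard of care, to prevent loss of autonomy". Section 4.3.2 turns this into a binary criterion: "Proportion of patients with a loss of autonomy evaluated by ADLs and IADLs on Day 14 and Day 28".

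The analysis rule is in section 6.3.6: "The analyses on the secondary endpoints will be performed on intention-to-treat on available data, except for safety analysis". Section 6 defines the term: "Analysis on available data (AD): any missing value will be ignored". Section 6 also defines a missing-as-failure rule, but section 6.1 assigns it to the primary endpoint only.

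On deaths, section 6 states: "Participants who died, were lost to follow-up or withdrew consent will be included in the analysis". Nothing in the protocol gives a participant who died an ADL/IADL value or counts the death as loss of autonomy.

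On the Day 14 assessment, section 5.3.6 states: "Face-to-face visits shall be carried out in the participant's home by the trial's mobile team". Section 5.3.8 places the end visit of participants who were hospitalised 7 days after discharge. ADL/IADL does not appear in the visit content of 5.3.6 or 5.3.8, or in Table 1, so where and how it is collected is not fixed.

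**The concern.** Death is part of the primary endpoint, which the trial hopes to halve. If a drug saves lives, fewer participants are missing from the autonomy analysis in its arm than in the control arm, and the extra ones who are scored may be frail. The deaths they replace vanish from the control arm instead of counting as the worst outcome. Randomisation no longer protects such a comparison, because being scored depends on treatment.

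At stake is the reading of one efficacy objective. A drug that reduces deaths could show a smaller benefit on autonomy than it has. If those it saves are often dependent, it could show none, or apparent harm.

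**Working it through.** **The plan's own figures.** The protocol gives no rate or power for the autonomy endpoint. Its sample size, 169 per arm, is for the primary endpoint (section 6.2.1: up to 25% in control, halved to 12.5%, 80% power). A one-sided 0.025 test with continuity correction gives 168 per arm. The final level is an assumption, since the protocol gives none as a number. The sample size is not in dispute. At the planned rates, 169 × 0.25 ≈ 42 control and 169 × 0.125 ≈ 21 experimental participants are hospitalised or dead by Day 14.

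**Notation.** Per randomised participant, d is the proportion dead and L the proportion alive with loss of autonomy.
- Available data, only deaths missing: L / (1 − d)
- Death counted as loss (composite): d + L

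**Case 1: deaths and admissions both halved.** Assumed: deaths 5% vs 2.5%; admitted survivors 20% vs 10% (these add to the planned 25% and 12.5%); loss in 60% of admitted survivors and 10% of the others. All survivors are scored.
- Control: L = 0.20 × 0.6 + 0.75 × 0.1 = 0.195. Available data 0.195 / 0.95 = 20.5%; composite 0.05 + 0.195 = 24.5%.
- Drug: L = 0.10 × 0.6 + 0.875 × 0.1 = 0.1475. Available data 0.1475 / 0.975 = 15.1%; composite 0.025 + 0.1475 = 17.25%.
- Benefit: 5.4 points on available data, 7.25 on the composite.

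**Case 2: only deaths differ.** Assumed: deaths 5% vs 2.5%; 10% loss in those who survive in either arm; loss in a proportion q of those saved.
- Control: L = 0.95 × 0.10 = 0.095. Available data 10.0%; composite 14.5%.
- Drug: L = 0.095 + 0.025q. Available data L / 0.975; composite 0.025 + L.

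| q | Available data, control vs drug | Composite, control vs drug |
|---|---|---|
| 10% | 10.0% vs 10.0% | 14.5% vs 12.25% |
| 30% | 10.0% vs 10.5% | 14.5% vs 12.75% |
| 80% | 10.0% vs 11.8% | 14.5% vs 14.0% |

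The available-data contrast is nil when those saved have the same loss rate as other survivors, and turns against the drug when their rate is higher. With deaths 10% vs 5% and q = 80%, it is 10.0% vs 13.7%, against 19.0% vs 18.0%.

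**Case 3: some in-patients also unscored on Day 14.** Inputs as in case 1, varying the share of admitted survivors who are scored. If half are scored:
- Control: (0.10 × 0.6 + 0.075) / (1 − 0.05 − 0.10) = 0.135 / 0.85 = 15.9%.
- Drug: (0.05 × 0.6 + 0.0875) / (1 − 0.025 − 0.05) = 0.1175 / 0.925 = 12.7%.

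| Admitted survivors scored | Available data | Benefit shown |
|---|---|---|
| All | 20.5% vs 15.1% | 5.4 points |
| Half | 15.9% vs 12.7% | 3.2 points |
| None | 10.0% vs 10.0% | 0 |

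The composite benefit, with in-patients' true status known, is 7.25 points in every row.

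**The case against.** **Detail is left to the SAP, and deaths are said to be included.** Section 6.3.1 defers details of secondary analyses, and section 6 keeps those who died in the analysis. Neither cures the problem. The protocol itself fixes the missing-data rule in 6.3.6, and membership of the analysis set does not supply a score.

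**The survivors' question is legitimate.** In case 2 with q = 80%, dependent survivors per randomised participant do rise, from 9.5% to 11.5%, so a worse result truthfully describes survivors. Deaths, hospitalisations and intensive care admissions are also reported as separate criteria. This stands as a reason to keep the survivors-only figure as a description. It does not make that figure a sound randomised comparison for an objective of preventing loss of autonomy.

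**The effect may be small.** Case 1 shows attenuation, with the direction intact. The reversal in case 2 needs those saved to be more dependent than other survivors. 80% is a strong assumption when enrolment requires an ambulatory person and excludes a Rockwood score of 7 or more. The composite benefit that is reversed there is only 0.5 point, less than one participant at 169 per arm. This stands, and limits the weight of the point.

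**In-patients.** A reader might infer from the home-visit wording that everyone in hospital on Day 14 goes unscored, and that the whole benefit is then lost. The documents do not support this. They do not say where ADL/IADL is collected, Table 1 marks Day 14 as a telephone call, and section 5.4.3.2 requires follow-up of serious adverse events, which include hospitalisation. A telephone or proxy score is not ruled out. Losing the whole benefit would also need every participant admitted since Day 0 to be dead or unscored on Day 14, although those already discharged can be assessed. What remains is a possibility: no in-hospital assessment is described, and the remote substitute in 5.3.9 is limited to participants whose course is clinically reassuring.

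**Conclusion.** The point holds for deaths. Sections 6.3.6 and 6 together remove participants who die from the loss-of-autonomy proportion at Day 14 and Day 28, leaving a comparison among survivors that treatment can select. Under the assumed rates, the benefit shown runs from 5.4 points instead of 7.25 (case 1) to an apparent 1.8-point harm where the composite shows a 0.5-point benefit (case 2, q = 80%). The distortion can therefore be attenuation, masking or reversal. Which one applies depends on death and ADL rates that the protocol does not give, so it cannot be said that a benefit will be hidden or reversed.

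Unscored in-patients would add to the distortion at Day 14, but that is an inference from the visit description. They would add less at Day 28, because hospitalised survivors have an end visit after discharge.

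The matter concerns one secondary endpoint without its own power calculation and does not touch the primary analysis. It is worth correcting because the rule is fixed in the protocol and the remedy is cheap.

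**What to change.** - In 4.3.2 and 6.3.6, define the endpoint as death or loss of autonomy at Day 14 and Day 28, with death scored as loss.
- Report deaths and loss of autonomy among survivors separately beside it, and keep the survivors-only available-data proportion as supportive.
- State that ADL/IADL for participants in hospital on Day 14 is sought by telephone from the participant, a relative or the ward.
- Score in-patients whose ADL/IADL cannot be obtained as loss only in a sensitivity analysis. Doing so in the main analysis would build the primary event into a functional endpoint.

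The cost is wording in two sections and one telephone call for each participant in hospital on Day 14. The small downside is that the endpoint mixes death with dependence, which is why the components must be shown.

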### 6.3.7 Safety analysis

The analysis will be performed on participants having taken at least one dose of randomisation treatment on available data, from D0 to D14 and D28.

Adverse events will be described through SOC and PT levels of MedDRA classification (last version at time of database freezing).

The incidence of adverse events will be described in terms of nature, causality, severity, intensity.

The incidence of adverse events related to randomisation treatment discontinuation or dosage modification will be described and compared between arms.

Safety analysis will be performed in compliance with the recommendations of the Consort Statement on harm.

## 7 Governance

### 7.1 Sponsor

The co-sponsors are to be:

- CHU de for activities occurring within France
- Inserm-ANRS, for activities occurring within Africa (which shall be described in the ancillary protocols).

The Inserm 1219 team has held numerous international studies sponsored by the two sponsors. This common experience guarantees the fastest possible implementation of the study.

## **8 Monitoring**

### **8.1 Scientific Advisory Board**

- The Scientific Advisory Board (SAB) is to meet by teleconference every other week.
- It is to be composed of:
  - The coordinating investigator and the research coordinator, the senior methodologist, the senior statistician, the project manager and the monitoring advisor.
  - 3 experts in the areas of infectious diseases, clinical trial and immunological methods and the pharmacological monitoring of clinical trials.
  - One representative for the sponsor and for each partner institution.
- This guarantees that the trial is held in an appropriate manner at the scientific, clinical and ethical levels. That includes:
  - Checking that the team charged with the trial is observing protocol and ensuring the safety of participants
  - Guaranteeing the relevance of the trial's questions and the validity of its methods.
  - Making decisions regarding those necessary and relevant changes to the protocol.
  - Deciding whether to open or close trial sites.
  - Checking observance of the rules regarding access to data, reports and trial publications.
  - Ensuring liaison with the DSMB and the regulatory authorities.

## 8.2 Data & Safety Monitoring Board

- The Data & Safety Monitoring Board (DSMB) is to meet by teleconference every other week. In the interim, it shall be informed daily of the number of hospitalised and deceased participants.
- It shall be composed of three external, independent experts in the disciplines of infectious diseases, pharmacovigilance and suitable clinical trial methods, nominated by the sponsor.
- It is to oversee the general running of the trial, in order to protect the safety and interests of the participants. It shall provide advice on the conduct of the trial, pertaining to inclusion rates, quality of follow-up, adverse reactions, interim analyses of the main judgement criterion and recruitment of the required number of participants. It shall assist in making difficult decisions, which require an independent evaluation, while the trial is in progress.
- It shall have access to safety data, as well as any information justifying any change that affects the roll-out of the trial.

## 9 Sub-studies

Two sub-studies are in preparation. This chapter describes their objectives and methods. They shall be offered to a sub-group of participants. They shall be the subject of a specific consent. They shall only start once the main study is under way and functioning in a manner judged satisfactory by the SAB. The information and consent forms shall be submitted to the IRB for approval before the start of these sub-studies. Given the urgency of implementing the main study, this submission shall be postponed.

### 9.1 Immunological sub-study

The immunological sub-study has three explanatory objectives:

- evaluating the impact of study drugs on immunological parameters.
- identifying the immune biomarkers associated with clinical worsening.
- identifying the immune biomarkers associated with a change of the effect of those interventions evaluated.

In relation to the main study, it involves two things: (i) sampling of additional blood tubes on Day 0, Day 7 and Day 14 (additional 3ml); (ii) daily sampling of blood drops on a cotton swab (8 in total during the follow-up). This is only a gesture, yet whose enactment could prove difficult for certain people, or undesired by others in this particular context. It shall therefore be carried out by a sample of volunteers and subject to specific consent.

#### 9.1.1 Justification

The initial reports of patients heavily infected by CoV-2 of SARS have shown an increase in pro-inflammatory cytokines associated with severe pulmonary lesions and a transfer to Intensive Care Units (69). Patients infected with SARS CoV and MERS CoV have developed CD4+ and CD8+ T cells as well as B cells specific responses (70). As a result, even though the mechanisms and consequences of the hyperinflammation may be unknown, it is possible to posit the theory that the premature changes in some of these markers could be predictive of future clinical evolution. Furthermore, the reduction in hyperinflammation could be one of the mechanisms for which intervening could have a clinical impact. Finally, the presence of hyperinflammation could influence the effect of intervening, as is the case with IL-1 effect blockade in septicemia (71).

